Thanks to microperimetry, it is now possible to study more precisely the functional impairment in various retinal pathologies [20], especially with optical coherence tomography (OCT) scanning laser ophthalmoscope (SLO) microperimetry which couples microperimetry data with OCT data [21]. A retrospective study using microperimetry by Tadayoni et al. found that ILM peeling may reduce retinal sensitivity and significantly increase the incidence of microscotomas after macular surgery [22]. These abnormalities may explain the visual discomfort reported by some patients undergoing ERM and are not detected by measurement of VA and/or visual field. In a retrospective study, Deltour et al. found that active peeling was associated with more numerous and deeper microscotomas than spontaneous peeling [23]. Their localization seemed to fit the gripping areas of the ERM and ILM.

The purpose of this study is to clarify the benefit/risks ratio of the ILM peeling during ERM surgery. Microperimetry takes a central role to search for the number and type of microscotomas induced by the surgery. This study also further refines the analysis of anatomical abnormalities visualized by spectral domain optical coherence tomography (SD-OCT) and their correlation with the visual outcome of this surgery and the presence of microscotomas.

If active ILM peeling is significantly associated with more microscotomas, it may contraindicate the ILM peeling during primitive idiopathic ERM surgery.

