**Fig. 1 Fig1:**
[figure not shown]
Study diagram

On the day of the surgery (D-0), for phakic eyes with cataract, phacoemulsification is performed. For all patients, central and peripheral vitrectomy (25 gauge) and dissection of the ERM are performed. Membraneblue-Dual® is used to stain ILM for an exposure time of 1 min. Intraoperative pictures are then taken to see the possible spontaneous ILM peeling: if ILM remains, the patient is randomized in the operating room in the “no peeling” group or in the “active peeling” group. In the “active peeling” group, the ILM peeling is performed on at least two papillary diameters around the fovea, which corresponds to a “circle” of four papillary diameters.

At the end of the surgery, the retinal periphery is checked. The operation is filmed and the anonymous videos are centralized in Nantes to compare the appearance of microscotomas and grip areas of the ERM and ILM seen by video and photo. For about 30% of patients [29], the ILM is spontaneously peeled off. These patients are not randomized but they can be included, if they want it, in the ancillary study. This ancillary study has the same follow-up visits (at 1, 6, and 12 months) with the same examinations as the principal study.

A total of three follow-up visits are planned over a time span of 12 months postoperatively (at 1, 6, and 12 months). At each visit, the following are performed: VA on the ETDRS scale; near vision (Parinaud scale); SD-OCT; microscopic examination of the eye; microperimetry; fundus photography and postoperative “Patient discomfort” questionnaire; biomicroscopic examination of the anterior segment; retinal photography; and an assessment of adverse events (AE). The schedule of the trial is shown in Table 2. To avoid any bias, the follow-up visits are made by masked ophthalmologists and orthoptists who do not know if ILM was actively peeled off.

**Table 2 Tab2:** Study schedule

Actions	Inclusion visit D-90 and D-7	D0 (Surgery)	M1 (30days±7days starting D0)	M6 (6 months ± 15 days starting D0)	M12 (12 months ± 15 days starting D0) End of study
Patient information	X				
Informed consent	X				
History (medications taken…)	X				
Randomization		X			
Surgery		X			
ETDRS visual acuity score and near vision (Parinaud)	X		X	X	X
Evaluation of the appearance of the lens at the slit lamp	X				
Biomicroscopic examination of the anterior segment	X		X	X	X
Fundus	X		X	X	X
SD OCT	X		X	X	X
OCT/SLO: microperimetry	X		X	X	X
Retinal photography	X		X	X	X

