#### Outcomes {12}

The main endpoint is the difference between the number of microscotomas (sensitivity < 10 dB) found before surgery and the number of microscotomas found at 6 months (number in the range of 0–29).

The secondary endpoints are:
VA measured on the ETDRS scale and near vision (Parinaud) (at inclusion visit and 1, 6, and 12 months after surgery)Number and types of microscotomas by microperimetry (before and after surgery)Mean retinal sensitivity by microperimetry before and after surgery (at 1, 6, and 12 months)Patient visual discomfort questionnaire: symptoms and subjective improvement before and after surgery (at 1, 6, and 12 months)Incidence of changes of the retinal nerve fiber layer SD by OCT analysis (B scan and C scan) before and after surgerySinusoid (IS/OS) line disruption by OCT analysis (B scan and C scan) before and after surgeryMean retinal thickness by OCT analysis (B scan) before and after surgeryRetinal nerve fiber layer thickness by OCT analysis (B scan) before and after surgeryOuter segment photoreceptor thickness by OCT analysis (B scan) before and after surgeryRecurrence of ERM by OCT analysis (B scan and C Scan)Operative report and the video recording area of ERM and ILM gripping (study of the correlation with the microscotoma(s).

The endpoints of the ancillary studies are:
The main criterion: the difference between the number of microscotomas (sensitivity < 10 dB) found before surgery and the number of microscotomas found at 6 months (number in the range of 0–29).VA measured on the ETDRS scale and near vision (Parinaud) (at inclusion visit and 1, 6, and 12 months after surgery)Number and types of microscotomas by microperimetry (before and after surgery)Mean retinal sensitivity by microperimetry before and after surgery (at 1, 6, and 12 months)Patient visual discomfort questionnaire: symptoms and subjective improvement before and after surgery (at 1, 6, and 12 months)Incidence of changes of the retinal nerve fiber layer SD by OCT analysis (B scan and C scan) before and after surgerySinusoid (IS/OS) line disruption by OCT analysis (B scan and C scan) before and after surgeryMean retinal thickness by OCT analysis (B scan) before and after surgeryRetinal nerve fiber layer thickness by OCT analysis (B scan) before and after surgeryOuter segment photoreceptor thickness by OCT analysis (B scan) before and after surgeryRecurrence of ERM by OCT analysis (B scan and C scan)

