#### Sample size {14}

A retrospective study conducted in the Department of Ophthalmology of the University Hospital of Nantes in 2013 [23] showed that of 11 patients who received active peeling, the number of microscotomas was 2.5 ± 3.1 preoperatively and 6.5 ± 7.3 at 1 month.

Based on the number of microscotomas found in the active peeling group in our retrospective study, with 80% power and a type I error of 5%, 100 patients are needed to highlight a halving of the number of microscotomas in the non-peeling group relative to the active peeling group (i.e. 6 ± 6 microscotomas average peeling in the active group compared to 3 ± 4.6 in the non-peeling group).

Usually, only very few patients do not attend their 6-month visit. However, the occurrence of EIGs (endophthalmitis, retinal detachment) may prevent the determination of the number of microscotomas at 6 months by microperimetry. Assuming that at most 5% of patients will be affected, 106 patients will be randomized, or 53 patients per group.

As all the patients with spontaneous peeling during surgery will not be randomized, > 106 have to be enrolled. The estimated number of spontaneous peeling was initially 30% [23], so the number of patients enrolled were thought to be 156. During the study, we noted that spontaneous peeling occurred in 50.2% of cases and so the number of patients to enroll in the study has been revised to 222 patients (amendment to the protocol in December 2017).

The ability of the six centers to recruit is estimated to be 120 patients per year (30 patients per center), given that the primitive ERM is a common disease.

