### Data collection and management

#### Plans for assessment and collections of outcomes: description of the parameters for evaluating efficacy {18a}

Here are detailed the parameters to assess effectiveness:

First, the microperimetry is a non-invasive test that allows a real-time, qualitative, and quantitative assessment of visual function. Microperimetry is introduced in routine clinical diagnostic procedure which, with extreme precision, defines the retinal attachment point and the threshold of differential sensitivity of the retina. Retinal sensitivity is better within 3° around the fixing point, with a mean foveal threshold of 20 dB, and a 0.275 dB mean decrement for each 10°. Scotomas are defined as absolute (if the patient does not perceive the maximum stimulation, the sensitivity is 0 dB) or relative (reduction of retinal sensitivity compared to normal values is < 10 dB). Assessing retinal function with this tool provides valuable clinical and pathophysiological information. These abnormalities could explain the hitherto non-assessable visual discomfort by conventional methods reported by some patients undergoing epiretinal membrane or macular hole surgery.

For all patients and to standardize the measurement, we use the “Ivana” protocol directed by the ophthalmology service of Lariboisière: a fixation target consisting of a red cross 2° in diameter, a white background monochromatic 4 asb, stimulus size Goldmann II with a projection time of 200 ms and a grid of 29 measurement points in the central 9° (centered on the fovea) with a 4–2-1 “double staircase” threshold strategy. Automatic “eye-tracking” will record eye movements throughout the exam. In addition, we will conduct topographies of the macular area in spectral OCT/SLO combined with microperimetry (OPKO/OTI, Miami, FL, USA).

Second, the scale of evaluation of the ETDRS VA will be performed by a masked orthoptist so as not to influence the patient’s response.

Third, a “Patient discomfort” questionnaire made by the ophthalmologist team will be given to the patient to evaluate their symptoms before and after the surgery.

Fourth, the SD-OCT will allow a precise anatomical pre- and postoperative analysis of the macula. The projected sequences include:
RASTER (B scan): 1024 A scans; 25 sections (nine frames) spaced by 240 μm, covering an area of 20° × 20°FRONTAL acquisition (C scan): 512 A scans; 193 sections (16 frames) spaced by 30 μm, covering an area of 20° × 20°.

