#### Data management {19}

For each patient, a case report form (CRF) is created, which includes the data necessary to ensure compliance with the protocol and all data necessary for the statistical analysis and identify major protocol deviations. Data collection is done directly by the investigator or clinical research associate (CRA) in charge of the study, using an electronic CRF (eCRF) developed by the Promotion Department of the University Hospital of Nantes with ENNOV Clinical. The data are encoded to keep the identities of the patients confidential.

The collection of clinical data will be based on the establishment of a clinical database and the creation of input screens for image capture. The surgery videos are transferred anonymously on USB keys provided by the sponsor. A surgeon at the Department of Ophthalmology will note the gripping areas of the ERM in parallel with what the investigator has already noted.

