### Statistical methods

#### Statistical methods for primary and secondary outcomes {20a}

The variables measured at baseline are described for all patients in both group by numbers and percentages for each category for categorical variables and the minimum, maximum, average, standard deviation, and quartiles for the quantitative variables.

The primary endpoint is the difference between the number of microscotomas measured before surgery and the number of microscotomas measured at 6 months (a number in the range of 0–29). The mean difference is calculated in each of the two groups and compared using a mixed linear regression model to take into account the stratification of the randomization of the center (the center will be considered as a random effect) and adjustment for the preoperative number of microscotomas. Then, center-effect is analyzed with a fixed-effect model.

The following secondary endpoints are analyzed using a mixed linear regression model: comparison of the number of microscotomas in the two groups between preoperative visit and at 12 months; description and comparison of the type of microscotomas before surgery and at 1, 6, and 12 months; comparison of changes in mean visual acuity and in mean retinal sensitivity; study of the association between the presence of SANFL or DONFL with the number of microscotomas; comparison of the OCT B scan; and study of the associations between data in the OCT B scan and VA and between data in the OCT B scan and the presence of microscotomas.

The comparison between the two groups in the frequency of symptoms (blurred vision, metamorphopsia, relative scotoma, diplopia and micropsia), the comparison of the percentage of abnormalities detectable by OCT in front of the layer of optical fibers, and the comparison of the percentage of recurrence of the ERM at 12 months between the two groups are analyzed by Chi-square tests stratified on the center.

The correlation between VA and retinal sensitivity (the central point and the average of the five most central points) are analyzed according to the measurement of Pearson or Spearman’s correlation coefficients.

In addition, a description for each group of the number of microscotomas that are not located in a gripping area of the ERM and the ILM (at 1 month and 6 months) and a description of the outcome (disappearance/persistence) of microscotomas that existed before the surgery at 1 and 6 months is done.

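### The stated grip-location analysis counts microscotomas outside gripping areas without a denominator and includes preoperative ones, so it cannot by itself answer the listed correlation question, and its arms are not comparable

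*Protocol article*

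**What the plan says.** All references are to the Protocol article.

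- **Hypothesis.** Background and rationale {6a} reports of the microscotomas in a retrospective study: "Their localization seemed to fit the gripping areas of the ERM and ILM".
- **Endpoint.** Outcomes {12} lists as a secondary endpoint: "Operative report and the video recording area of ERM and ILM gripping (study of the correlation with the microscotoma(s"). Interventions description {11a} says the videos are centralized for this comparison.
- **Analysis.** For 1 and 6 months, Statistical methods {20a} plans this: "description for each group of the number of microscotomas that are not located in a gripping area of the ERM and the ILM". The same sentence adds "a description of the outcome (disappearance/persistence) of microscotomas that existed before the surgery at 1 and 6 months is done". No other analysis in that section uses grip location.
- **Measurement.** Section {18a} fixes "a grid of 29 measurement points in the central 9° (centered on the fovea"). A microscotoma is a sensitivity below 10 dB.
- **Arms.** In the active arm "the ILM peeling is performed on at least two papillary diameters around the fovea" (Interventions description {11a}). In the other arm the ILM is not peeled (Implementation {16c}).
- **Reading of grips.** Section {18a} has an ophthalmologist in Nantes look for both ERM and ILM gripping areas. Data management {19} says: "A surgeon at the Department of Ophthalmology will note the gripping areas of the ERM in parallel with what the investigator has already noted", which names the ERM only.

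**The concern.** Whether microscotomas cluster where membranes were gripped is a question about rates: how often a tested point becomes a microscotoma inside a grip compared with outside one. The planned number departs from that in three ways.

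1. It is a raw count in one zone. The number of tested points inside and outside the grips does not enter.
2. It is not restricted to new microscotomas. One that existed before surgery cannot have been caused by gripping. The separate description of persistence is not split by grip location, so it cannot be used to correct the count.
3. ILM gripping from active peeling occurs in one arm only. Where those grips cover points the ERM grips did not, fewer points are left to count in that arm.

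At stake is the mechanistic reading of the videos. A small outside-grip count could be taken as support for the grip explanation, and persisting preoperative microscotomas as evidence against it, when neither inference follows.

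**Working it through.** **The plan's own figure.** The outside-grip description has no figure of its own. The sample size reproduces and is not affected. The pooled SD is √((6² + 4.6²)/2) = 5.346. With a difference of 3, two-sided 5% (sidedness assumed) and 80% power, the normal approximation gives 50 per arm, 100 in total. Then 100/0.95 = 105.3, so 106 (Sample size {14}).

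**Inputs.** From the document: 29 points per eye; planned means of 6 (active) and 3 (no peeling), read here as counts; and, in 11 retrospective active-peeling patients, "the number of microscotomas was 2.5 ± 3.1 preoperatively and 6.5 ± 7.3 at 1 month". Assumed, because the document gives no grip coverage: g points under ERM grips in both arms, and k further points under ILM grips in the active arm.

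**Step 1: no denominator.** Suppose an eye has 6 microscotomas, 4 outside and 2 inside grips. The inside/outside rate ratio is (2/G) ÷ (4/(29 − G)), where G is the total number of gripped points.

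| G | Calculation | Ratio |
|---|---|---|
| 3 | (2/3)/(4/26) | 4.33 |
| 6 | (2/6)/(4/23) | 1.92 |
| 10 | (2/10)/(4/19) | 0.95 |
| 15 | (2/15)/(4/14) | 0.47 |

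The same count of 4 fits a strong association, none, or a reversed one.

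**Step 2: preoperative microscotomas.** If all of them persist (an upper limit on persistence), their share of the total count is 2.5/6.5 = 38% in the retrospective series. Against the planned means it is 2.5/6 = 42% in the active arm and 2.5/3 = 83% without peeling. The dilution would therefore differ by arm. The share within the outside-grip count can be larger still. If every new microscotoma lay inside a grip and the 2.5 old ones were spread evenly over the grid, then with g = 3 and no ILM grips the outside count would still average 2.5 × 26/29 = 2.24.

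**Step 3: comparability of the arms.** If location is unrelated to gripping, the expected outside count is mean × (29 − g − k)/29, with k = 0 in the no-peeling arm. Take g = 3 and k = 2 to 8.

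| Scenario | No peeling | Active, k = 2 | Active, k = 8 | Active vs no peeling |
|---|---|---|---|---|
| Mean 3 in both arms | 3 × 26/29 = 2.69 | 3 × 24/29 = 2.48 | 3 × 18/29 = 1.86 | 8% to 31% lower |
| Planned 6 vs 3 | 2.69 | 6 × 24/29 = 4.97 | 6 × 18/29 = 3.72 | 85% to 38% higher |

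In the second row the true ratio of 2.0 is pulled down to 1.85 (k = 2) or 1.38 (k = 8). The active count would fall below the other arm only if 6 × (26 − k) < 3 × 26, that is k > 13. With g = 2, 4 or 6 the threshold (29 − g)/2 is 13.5, 12.5 or 11.5. If ILM grips lie wholly within ERM grips, k = 0 and there is no bias.

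**The case against.** A reader might infer that the active arm's outside-grip count must be lower by construction. The document does not support that. It requires equal rates per point in the two arms and ILM grips that extend beyond the ERM grips. The protocol plans for unequal rates, and Step 3 shows the active count is then higher over the whole coverage range used. Only a downward bias remains.

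Further points in the plan's favour:

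- **It is only a description.** Section {20a} states no test, no contrast between arms and no causal conclusion for it. This stands, and it limits the weight of the point.
- **Preoperative microscotomas are described separately at the same visits.** This stands in part: their persistence will be known rather than assumed. As worded, it will not be known by grip location, and that is what the count would need.
- **The inside-grip count follows by subtraction from the total.** True, but a rate still needs the number of points in each zone.
- **A fuller protocol or analysis plan, not shown, may add denominators or a separate correlation analysis.** Possible, and the absence of such detail is not the finding. The finding is that the quantity the article does fix does not match the endpoint it lists.
- **The ERM-only wording in Data management {19} may be a slip.** Quite possibly. It still needs reconciling, because {12}, {18a} and {20a} all rely on ILM grips.

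**Conclusion.** The point holds for a descriptive secondary question. The only grip-location analysis stated in {20a} lacks a denominator and, as worded, mixes old with new microscotomas. It cannot by itself answer the correlation listed in {12}. Its arms are not comparable wherever ILM grips add area: the bias is downward for the active arm, 8% to 31% with 3 ERM-gripped and 2 to 8 additional ILM-gripped points at equal rates, and zero if the grips overlap fully. All coverage figures are assumptions. The preoperative shares of 38%, 42% and 83% assume full persistence and rest on 11 retrospective patients. The primary endpoint, its analysis and the sample size are untouched.

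**What to change.** - Classify each of the 29 points per eye as inside an ERM grip, inside an ILM grip, or outside any grip, reading the video without knowledge of the microperimetry.
- Among points at or above 10 dB before surgery, report by arm and zone the proportion falling below 10 dB at 1 and 6 months.
- Compare inside with outside within eye, using a method that accounts for clustering of points by eye, for example a logistic model with a random eye effect. Present the result as an association, because grip sites are not randomized.
- Keep the persistence description and split it by the same zones.
- Reconcile Data management {19} with {12}, {18a} and {20a} on whether ILM grips are noted as well as ERM grips.

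The cost is a little more coding of grip position on the grid, plus programming. Placing microscotomas inside or outside a grip already requires overlaying the grip map on the grid, and the point-level thresholds and videos are already collected. No visit, test or patient is added.

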#### Interim analyses {21b}

No interim analysis will be performed and no early stopping rule for futility will be proposed.

#### Methods for additional analyses (e.g. subgroup analyses) {20b}

Analyses for the ancillary study. The patients with spontaneous peeling are not randomized and are compared to the “active peeling” group.

The main criterion is, like in the main study, the difference between the number of microscotomas (sensitivity < 10 dB) found before surgery and the number of microscotomas found at 6 months (number in the range of 0–29). The other endpoints are the same as the secondary endpoints of the main study, without the analysis of the video recording.

Mixed linear regressions models and stratified Chi-square test are used for comparisons.

#### Methods in analysis to handle protocol non-adherence and any statistical methods to handle missing data {20c}

As already stated very few patients generally refuse to attend the visit at 6 months. However, for the primary endpoint, in case of no show or of SAE (endophthalmitis, including retinal detachment), missing values will be dealt with multiple imputation.

Secondary endpoints: there will be no attribution of missing data for the secondary endpoints.

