## Introduction

### Background and rationale {6a}

The epiretinal membrane (ERM) is a degenerative condition associated with age, characterized by a fibrocellular proliferation developing at the surface of the macula. The treatment of symptomatic ERM remains surgical removal including a vitrectomy followed by peeling of the ERM using a microforceps. As the internal limiting membrane (ILM) is adherent to the ERM, it is sometimes removed with it (spontaneous peeling). If it remains in place, the relevance of ILM intentional removal (“active peeling”) remains controversial.

The surgeons often peel the ILM as an adjuvant action expected to increase the success rate of the surgery. Some observational studies found that the risk of recurrence is reduced from 7%–23% without ILM peeling to 0%–4% with ILM peeling during idiopathic ERM removal [1–6]. In a meta-analysis, Azuma et al. [7] found a significant reduction of recurrence rate in case of ILM peeling during idiopathic ERM surgery (odds ratio 0.25; 95% confidence interval 0.12–0.49). Two randomized clinical trials compared ILM peeling or not: De Novelli et al. found a similar difference after 6 months (4% of recurrence with ILM peeling and 17% without) but did not reach significance; Tranos et al. did not found any recurrence in both groups after 12 months [8]. In case of recurrent ERM, vision is impaired in only half of the patients; if visual loss does occur, a second ERM surgery is possible [9].

The peeling of the ILM does not alter nor improve postoperative visual acuity (VA) [7–11]. This additional procedure lengthens the operation, increases the surgical risks (phototraumatism, retinal tear, central or eccentric macular hole) [12–14] and the risk of histological disorganization of the retina [15], which can result in one or more microscotomas with possible definitive visual discomfort for the patients. ILM is formed by Muller cells end-feet and ILM peeling results in significant damage of Muller cells [16]. Swelling of the arcuate fiber layer (SANFL) [17] and dissociated optic nerve fiber layer (DONFL) [18, 19] are well-described retinal changes due to ILM peeling but no impairment of VA has been linked to these findings.

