#### Plan to promote participant retention and complete {18b}

In our current practice, we have noticed that very few patients refuse to attend the visit at 6 months that corresponds to the visit of the main objective (Fig. 1). A letter to remind them of the follow-up visit is sent 2 months before it. However, in case of no show or of serious adverse event (SAE; endophthalmitis, including retinal detachment), missing values for the primary endpoint will be dealt with multiple imputation*.* For the secondary endpoints, there will be no attribution of missing data.

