The level of statistical significance is set at 0.05. Statistical analysis will be conducted in SAS software.

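### Eyes that a surgical complication makes untestable are imputed like missed visits, which can understate harm of peeling if such complications are more frequent in the peeling arm

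*Protocol article*

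**What the plan says.** Section 20c of the protocol article sets the missing-data rule for the primary endpoint, the change in the number of microscotomas from before surgery to 6 months: "in case of no show or of SAE (endophthalmitis, including retinal detachment), missing values will be dealt with multiple imputation". Section 18b gives the same rule, again for no-shows and serious adverse events (SAEs) together: "missing values for the primary endpoint will be dealt with multiple imputation". Missing secondary endpoints are not imputed.

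The sample size section (14) explains how the SAEs matter. They "may prevent the determination of the number of microscotomas at 6 months by microperimetry", and the allowance for them is: "Assuming that at most 5% of patients will be affected, 106 patients will be randomized, or 53 patients per group". The background section (6a) says that peeling "increases the surgical risks (phototraumatism, retinal tear, central or eccentric macular hole".

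**The concern.** The rule joins two reasons for missing data. A missed visit may tell little about the eye. A count that is missing because of endophthalmitis or retinal detachment is missing for a reason tied to the condition of the retina, which is what the endpoint measures. Section 34's heading in the article (18a) scores a point as 0 dB when the brightest stimulus is not seen, and 0 dB lies below the 10 dB microscotoma threshold. An eye that had lost macular function would therefore lie near the bad end of the 0 to 29 scale.

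Multiple imputation as usually done assumes missing at random and would place such an eye among the tested eyes of its arm. If these complications occurred more often with peeling, the primary comparison would understate harm. That matters because the trial is meant to judge benefit against risk, and its result may be used to advise against peeling.

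**Working it through.** **1. The plan's own figure.** Section 14 plans on "6 ± 6 microscotomas average peeling in the active group compared to 3 ± 4.6 in the non-peeling group", 80% power and a 5% type I error; section 20a adds "The level of statistical significance is set at 0.05". Sidedness is not stated.

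- Pooled SD = √((6² + 4.6²)/2) = 5.35.
- A two-sided test for a difference of 3 needs 50 per arm, 100 in all. One-sided would need 80, so two-sided is taken.
- 100/0.95 = 105.3, rounded up to 106, or 53 per arm. The stated size reproduces. Power at 53 per arm is 0.82.

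**2. How many eyes.** The adverse event section (22) expects retinal detachment in 3% and endophthalmitis in 1 to 3 per 1000, for the surgery as a whole.

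- 106 × 0.031 = 3.3 and 106 × 0.033 = 3.5 eyes.
- The 5% ceiling gives 106 × 0.05 = 5.3 eyes.

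So about 3 to 5 eyes, if every such event left the eye untestable.

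**3. Effect on the difference.** Assumptions: imputed eyes take their own arm's mean (6 or 3), baseline counts are balanced, and an untestable eye would otherwise score S. With k such eyes in the peeling arm and j in the other:

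difference = 3 + [(S − 6)k − (S − 3)j]/53

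Under imputation the difference stays at 3.0 whatever k and j are. Otherwise:

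| k vs j | S = 10 | S = 15 | S = 20 | S = 29 |
|---|---|---|---|---|
| 2 vs 2 | 2.89 | 2.89 | 2.89 | 2.89 |
| 3 vs 2 | 2.96 | 3.06 | 3.15 | 3.32 |
| 3 vs 0 | 3.23 | 3.51 | 3.79 | 4.30 |
| 5 vs 0 | 3.38 | 3.85 | 4.32 | 5.17 |
| 0 vs 2 | 2.74 | 2.55 | 2.36 | 2.02 |

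For example, 3 vs 0 at S = 29 gives 3 + 69/53 = 4.30.

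**4. Which form of alternative analysis.** Putting 29 into the linear model for 5% of each arm raises the SD from 5.35 to 7.47 and cuts power from 0.82 to about 0.50, so it is a poor main analysis.

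Simulation of alternatives: 53 per arm, negative-binomial counts with the planning means and SDs, capped at 29, complete cases standing in for imputation, unadjusted tests.

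- 5% untestable in each arm: a worst-rank test has power 0.91. A rank test on complete cases has 0.95. The advantage over the linear model's 0.82 comes from ranking skewed counts, not from the handling of untestable eyes.
- No effect in tested eyes, assumed 5% vs 1% untestable: worst-rank rejects in about 6% of trials, close to its nominal level.
- Requiring both analyses to be significant: about 2% rejection in that second scenario, and power about 0.80 instead of 0.82 at the planned effect with 5% in each arm.

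**The case against.** A reader might infer that the plan hides harm of peeling. The article does not support that. It gives no complication rate by arm. The risks that it says peeling raises are phototraumatism, retinal tear and macular hole; neither SAE in the missing-data rule is on that list, although a tear can lead to detachment. Both arms have vitrectomy and membrane dissection, and the rates in section 22 are for the surgery overall. With balanced events the shift is negligible and slightly in the other direction. This objection stands and makes the direction conditional.

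The sample size section says only that the events may prevent the measurement. A treated eye that can be tested at 6 months enters with its own count, so 29 for every affected eye is a worst case. This also stands, which is why S is varied in the working.

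The imputation model is not described and could use SAE status or a shift; an article may leave this to the full protocol or analysis plan. That stands against any claim that the model is wrong or that no sensitivity analysis exists. It does not remove the point, because the article does fix a single rule for both reasons.

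Finally, every SAE requires a report, so the events stay in the trial's record. Any masking would be confined to the primary endpoint.

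**Conclusion.** The point holds in a limited form. One imputation rule is stated for two reasons for missing data, and the article itself recognises that one of them is caused by the complication. Under missing-at-random imputation about 3 to 5 of 106 eyes would be counted like tested eyes. With untestable eyes scored 29, the difference would be understated by about 0.3 (3 vs 2 eyes) to 1.3 (3 vs 0), and by 2.2 in the extreme case of 5 vs 0, against a target of 3. The shift is about −0.1 with 2 vs 2 eyes, and the bias reverses if the excess lies in the no-peeling arm.

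These sizes rest on assumed splits, assumed scores for untestable eyes, and planning counts used in place of the change score. The point should be fixed, but it is not critical to the trial.

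**What to change.** Keep multiple imputation for the primary analysis and for no-shows. Record in the eCRF why each 6-month count is missing. Before unblinding, pre-specify one sensitivity analysis in which eyes untestable because of a surgical complication take an unfavourable value: either a worst-rank analysis, or a delta-adjusted imputation over a stated range. Report it beside the primary result, with the number of such eyes by arm.

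Do not make it a second hurdle. Requiring both analyses to show harm would make harm harder to declare. Nor should worst-rank be chosen for its power, for the reason shown in step 4. On its own it would barely detect harm confined to a few untestable eyes, so the counts by arm are needed as well.

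The cost is one data field and one extra analysis, with no change in sample size. The drawback is that a rank result is not a mean difference, while a delta-adjusted result keeps the scale but depends on the chosen range.
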